***Spatially-defined motor function*** We use the Directional Hypokinesia task to assess two distinct forms of motor neglect – directional hypokinesia, i.e. relative slowing in the initiation of movements directed toward the affected side, and directional bradykinesia, i.e. relative slowing in the execution of movements directed toward the affected side of space [103]. The task measures movement initiation and execution times to targets that appear on the left or the right side of the screen. The task follows the exact procedure previously used for research with hemispatial neglect patients [57]. A black 1.4° fixation cross and two black 3° × 3° squares, one 12° to the left and one 12° to the right of the fixation cross, are on constant display (locations are re-expressed as affected and unaffected Visual Field, VF). Each trial is initiated by the participant pressing and holding a button with their index finger. After a time interval that varies randomly between 1500 ms and 3000 ms a black target (1.4° high “X”) appears inside one of the squares, in a pseudorandomized order, for 2000 ms. The target onset initiates the response window and the participant is required to release the button, touch the screen in the location where the target appeared, and then return their index finger to the button as fast as possible, which initiates the next trial. There are 30 trials per block. A touch screen is used to monitor the accuracy of pointing-to-target movements. The Reaction Times (RTs) to release the button after the target onset (Movement Initiation Time, MIT) are recorded, as well as time taken between releasing the button and touching the screen (Movement Execution Time, MET). There are three different hand Starting Positions (location of the button box): 25 cm to the left from body midline, central (aligned with the body midline), and 25 cm to the right from body midline (the locations are re-expressed as the affected, central, and unaffected side). Manipulating the hand Starting Position allows dissociation between perceptual component of the task (e.g., slower detection of the targets on the affected side) and the true directional hypokinesia. Participants perform each condition once with each hand in separate blocks, giving a total of 6 conditions (unaffected hand from the unaffected side, unaffected hand from the centre, unaffected hand from the affected side, affected hand from the unaffected side, affected hand from the centre, affected hand from the affected side). The order of the Starting Positions is counterbalanced between participants, with the only restriction that they alternate between the unaffected and the affected hand in each subsequent block to reduce fatigue.

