
We will calculate mean MITs and METs for each combination of VF in which the target appeared (affected and unaffected) and hand Starting Position (affected, central, and unaffected location), separately for each hand used to complete the task. Directional hypokinesia would be indicated by slower initiation of movements (MIT) towards the affected side of space, independent of which arm is used [57, 103, 104]. Directional bradykinesia would be indicated by slower movement execution times (MET) towards targets appearing in their affected side of space, even when using the unaffected arm.

To dissociate any signs of directional hypokinesia from potential mechanical constraints, two indices of directional hypokinesia will be derived based on the analyses described in previous research [57]. Movement pathways and indices are illustrated in Fig. 5. The first index (A) quantifies the difference in MITs to the targets in the affected vs. unaffected VF as a function of the direction of the movements, i.e,. reaching toward the affected side (from central Starting Position) relative to reaching toward the unaffected side (from affected Starting Position). Index A will be calculated as: [central Starting Position (MIT affected VF – MIT unaffected VF) – affected Starting Position (MIT affected VF – MIT unaffected VF)]. Thus, a larger value on this index will indicate greater directional hypokinesia. A potential drawback of Index A is that it involves planning a movement across body midline (from the affected Starting Position to the unaffected VF) that covers a longer distance and may be more difficult than other movement trajectories. Therefore, we will also derive a second index (B) that directly quantifies the relative slowing in the ability to initiate movements to the targets in the affected VF when making movements of the same physical length toward the affected side (from central Starting Position), versus toward the unaffected side (from affected Starting Position). Index B will be calculated as [central Starting Position (MIT affected VF) – affected Starting Position (MIT affected VF)]. Positive values on each index (A and B) would indicate hypokinesia for the affected side. Analogous indices A and B will be calculated for METs, and positive values of each index would indicate directional bradykinesia for the affected side.

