The Directional Hypokinesia task conditions performed with the affected and unaffected hand will be analyzed separately. After excluding incorrect and missed trials, we will use mean movement initiation times (MITs) and movement execution times (METs) for each combination of VF in which the target appeared and hand Starting Position to test if the participants with CRPS show signs of directional hypokinesia compared to the healthy controls. We will conduct two three-way ANOVAs on MITs for each hand with the following factors: Group (participants with CRPS, healthy controls), VF (affected, unaffected), and Starting Position (affected, central, unaffected). Significant interactions will be followed by four a-priori contrasts to test whether the participants with CRPS are slower to initiate movements toward the targets in their affected side of space (regardless of the direction of reaching movement required) and / or in the direction toward their affected side of space (regardless of the location of the target). Specifically, we will examine if participants with CRPS have slower MITs to the targets in the affected VF than in the unaffected VF; to the affected VF compared to healthy controls; to the affected VF from central compared to affected Starting Position; and to the affected VF from central Starting Position compared to healthy controls. Analogous analyses will be conducted on METs to test if participants with CRPS show signs of directional bradykinesia compared to healthy controls. We will also examine differences between Groups (participants with CRPS, healthy controls) on MITs and METs through separate contrasts for each index (A and B) of directional hypokinesia and bradykinesia. As further exploratory analyses we will examine how many participants with CRPS are impaired on both indices (A and B) of directional hypokinesia and bradykinesia by identifying which participants obtained positive A and B indices and by comparing each CPRS patient’s indices to the mean indices for healthy controls using Crawford t-tests [112].

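### The Directional Hypokinesia contrast meant to test target side irrespective of reach direction pools the central start, so it also picks up one third of any directional deficit

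*Protocol article*

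**What the plan says.** The task description (Computer-based/psychophysical tests, Spatially-defined motor function) puts the hand at three starts: "25 cm to the left from body midline, central (aligned with the body midline), and 25 cm to the right from body midline". It gives the reason: "Manipulating the hand Starting Position allows dissociation between perceptual component of the task" and true directional hypokinesia. Index A is described there as "reaching toward the affected side (from central Starting Position) relative to reaching toward the unaffected side (from affected Starting Position"), so the protocol itself codes reaches from the affected start as going toward the unaffected side.

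The RQ5 analysis section fits ANOVAs on movement initiation times (MIT) with Group, VF and "Starting Position (affected, central, unaffected"). Significant interactions lead to four a-priori contrasts with two aims: whether patients "are slower to initiate movements toward the targets in their affected side of space (regardless of the direction of reaching movement required") and/or "in the direction toward their affected side of space (regardless of the location of the target"). The contrasts are:

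1. "slower MITs to the targets in the affected VF than in the unaffected VF" (within patients, no start named);
2. affected VF, patients against controls (no start named);
3. "to the affected VF from central compared to affected Starting Position";
4. affected VF from the central start, patients against controls.

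Analogous analyses are planned for movement execution times (MET).

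**The concern.** Contrast 1 is the one that serves the target-side aim. Contrasts 3 and 4 each name a start and contrast 1 does not, so it averages over all three levels of the factor. One of those levels is the central start, where a target on the affected side is also a reach toward the affected side. A contrast that includes it cannot be independent of reach direction.

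At stake is the separation for which the starting positions are varied: slow response to targets on one side against slow initiation of movement toward that side. If only the second is present, contrast 1 can still be significant, and the report would list a target-side deficit as well as a directional one. Outcomes that differ from controls also feed the exploratory correlations under RQ5 and, in the first instance, the choice of predictors under RQ4.

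**Working it through.** The protocol gives no figure of its own on this point, so the check is on the geometry and on what each contrast estimates.

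**Inputs from the protocol.** Targets 12° either side of fixation; lateral starts 25 cm from the midline; 30 trials per block (all from the task description). Viewing distance 50 cm (Landmark task paragraph, which covers all the screen tasks). 42 participants with CRPS and 21 controls (Sample size and power calculation).

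**Geometry.** Target offset = 50 × tan 12° = 10.6 cm, so the lateral starts lie outside both targets. Lateral reach distances are 25 − 10.6 = 14.4 cm and 25 + 10.6 = 35.6 cm.

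| Start | Affected-VF target | Unaffected-VF target | VF difference |
|---|---|---|---|
| Affected | 14.4 cm, toward unaffected | 35.6 cm, toward unaffected | P |
| Central | 10.6 cm, toward affected | 10.6 cm, toward unaffected | P + D |
| Unaffected | 35.6 cm, toward affected | 14.4 cm, toward affected | P |

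P is the extra MIT for affected-side targets. D is the extra MIT for reaches toward the affected side.

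**What each planned quantity estimates.**

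- Contrast 1, all starts: (P + P + D + P)/3 = P + D/3.
- Contrast 2: P + 2D/3, plus any general slowing of patients.
- Contrast 3 and Index B: (P + D) − P = D.
- Contrast 4: P + D, plus general slowing.
- Index A: (P + D) − P = D.
- Contrast 1 on the two lateral starts only: (P + P)/2 = P.

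Direction is isolated three times. Target side is isolated by none of the planned quantities.

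**The gate.** If P = 0 and D > 0 in patients only, the VF difference is D at the central start and 0 at the other two. That is itself a Group × VF and a Group × VF × Starting Position interaction, so requiring a significant interaction does not block contrast 1.

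**Size before the gate.** Assumed, because the protocol gives no MIT variance: trial SD 100 ms, 15 trials per cell (30 per block split evenly), between-person SD 40 ms for D and 20–40 ms for P. True P = 0.

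- Cell noise: 100/√15 = 25.8 ms. Noise in contrast 1: 25.8 × √(2/3) = 21.1 ms.
- Between-person SD contributed by D/3: 40/3 = 13.3 ms.
- Person-level SD: √(20² + 13.3² + 21.1²) = 32.0 ms, or √(40² + 13.3² + 21.1²) = 47.1 ms.
- SE with n = 42: 4.9 or 7.3 ms.
- D = 60 ms: expectation 20 ms, 4.1 or 2.8 SEs from zero; significant in 98% or 77% of simulated studies.
- D = 30 ms: expectation 10 ms, 2.0 or 1.4 SEs; 51% or 27%.

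**Size after the gate** (simulated with 21 controls having D = 0): about 14–33% at D = 30 ms and 72–95% at D = 60 ms. The lateral-only contrast is significant in about 5%, ungated.

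**Check on a different scale.** With independent cell errors of SD 1 and no gate, D of 0.5, 0.75, 1.0 and 1.5 cell SDs gives rates of about 25%, 49%, 73% and 97% for contrast 1, against about 5% throughout without the central start.

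**The case against.** The strongest reply is that the main inference from this task is sound. The task is presented as a test of directional hypokinesia and bradykinesia. Contrast 3 and Indices A and B carry no P, and the indices are also compared between groups. Visuospatial attention has three tasks of its own (temporal order judgement, Landmark, Greyscales). A reader might infer that a directional deficit would be reported as a target-side deficit instead, or that the RQ5 account as a whole would be wrong. The documents do not support either: only one third of D leaks, the directional deficit still shows at full size, and the risk is one additional, smaller finding.

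Two more replies have force. Pooling is inferred from the absence of a named start, not stated; but the other likely choice, the central start alone, would give P + D, which is worse. And rates computed without the interaction gate overstate the problem at small D; the gated figures are the ones to use. They depend on which interaction opens the gate, and if any interaction with Group counted, the rate at D = 30 ms would be 23–42%.

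The direction contrasts use affected-VF targets only. Holding the target fixed does control for its location, so they are valid for D. The phrase "in the direction toward their affected side of space (regardless of the location of the target") nevertheless claims more than one target side can show. That the unaffected start is absent from the indices is a matter of efficiency, not an error.

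What the reply does not answer is that contrast 1 does not test what it is said to test, and nothing else in the plan does.

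**Conclusion.** The point holds in limited form. As written, contrast 1 estimates P + D/3 and is not independent of reach direction. That follows from the protocol's own geometry and from the plain reading that an unnamed start means all starts. Under the assumed variances, a purely directional deficit adds a spurious target-side result in about 14–33% of studies at D = 30 ms and 72–95% at D = 60 ms after the gate. The values of D and the SDs are assumptions, so the rates are illustrative; the D/3 term is not. The same confound applies to the analogous MET contrast.

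The scope is a secondary, baseline-only question. It would be wrong to infer a threat to the trial's efficacy conclusions: the primary outcomes do not involve this task, and the treatment analyses use only Indices A and B from it, which are free of the problem.

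**What to change.** Define the target-side contrast, for MIT and likewise for MET, as the affected-minus-unaffected VF difference averaged over the affected and unaffected Starting Positions only. From each of these starts both targets need a reach in the same direction, and over the pair each target is reached once across 14.4 cm and once across 35.6 cm, so distance balances. The contrast then estimates P alone.

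Drop or qualify the claim that the direction contrasts hold for any target location, since they use affected-VF targets only. Leave contrast 3 and Indices A and B as they are.

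The cost is wording; the task already collects trials at all three starts. The target-side contrast uses four of six cells, so its within-person noise SE rises from 21.1 to 25.8 ms (25.8/21.1 = 1.22, about 22%).

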##### Relationships between neuropsychological changes and clinical symptoms of CRPS

Correlation and regression analyses will be conducted to test relationships between neuropsychological changes (as measured by computer-based tasks) and clinical symptoms of CRPS (as measured by self-report questionnaires and clinical assessments). These analyses will depend on which outcomes show significant differences between participants with CRPS and healthy controls, thus they are exploratory.

## Discussion

Considering the poor overall response to conventional medical treatments for CRPS [113], it is important to seek novel methods of pain relief and symptoms improvement. PA is an emerging treatment that targets spatial attention deficits, has shown early promise as an intervention for CRPS, and might operate through different mechanisms to mirror visual feedback (another neurocognitive treatment for CRPS [22, 114]).

The ongoing trial that is described in this protocol is the first to investigate the effects of PA treatment on pain and CRPS symptom severity using a double-blind, randomized, and sham-controlled design in a patient sample that is large enough to detect a clinically significant reduction in pain. These aspects of our design, as well as stratified randomisation and intention to treat and per-protocol analyses will allow unbiased evaluation of a brief, low-cost treatment that can be easily self-administered by the participant in a home setting.

However, self-guided administration of the treatment might also be its limitation in the present study, as it prevents us from directly monitoring participants’ compliance. This is considered a necessary trade-off to test the treatment as it would be most likely integrated into CRPS management. Furthermore, opting for home-based treatment will aid the recruitment of a sufficient number of participants, who are drawn from a broad geographical area, as it would not be feasible for them to travel to the research centre for each treatment session, or for another researcher to repeatedly assess their compliance. We put in place several measures to encourage adherence to treatment, such as in-person training, instructions and guidance in multiple media, and easy access to advice. To avoid adding another layer of difficulty and increasing potential burden of treatment (especially for those participants who do not have very good technical competence), we decided against asking participants to video-record their treatment sessions. Thus, we rely solely on self-reported adherence, that is, recording the timing and completion of each treatment session in daily logbooks. This could limit the interpretation of our findings; however, we will evaluate them considering the possibility that participants may have not complied with the treatment regimen as expected.

While clearly defining our primary outcome measures, the trial includes a wide range of secondary outcome measures to assess the impact of treatment on pain and other clinical CRPS symptoms, as well as neuropsychological and emotional functioning, and symptoms’ interference with daily life. These measures will allow us to explore relationships between self-reported, clinical, and neuropsychological manifestations of CRPS from baseline data, independent of the primary research aim of testing the efficacy of PA.

Despite their informative value, large number of secondary outcomes might reduce the quality of data. To mitigate the potential impact of long duration and burden of research sessions, we composed a battery of assessments that would take no longer than 4 h to complete, including breaks between assessments. We also provide the participants with overnight accommodation near the research centre in cases when long travels are required, to minimise their fatigue during research sessions. In light of how little is known about cognitive changes in CRPS and effects of PA on these changes, broad battery of neuropsychological tests seems appropriate.

Furthermore, this research may identify potential individual differences accounting for the course of CRPS and response to treatment. The findings could provide an indication of how to identify the patients who are most likely to benefit from PA based on their cognitive and physical symptoms. This would inform subsequent research and therapies.

If PA brings benefits beyond that of the sham treatment on the primary outcome measures of the ongoing trial, this treatment should be developed as a recommended method to reduce pain and other CRPS symptoms. The study is likely to expand on our limited understanding of this debilitating condition and its neuropsychological components.

## Data Availability

There is no data associated with the current paper, which describes a protocol for a clinical trial that is in progress at the time of submission. All investigators will have access to the final dataset. Anonymised participant-level data from the trial will be stored using the Open Science Framework repository and access will be granted upon request. Access shall be requested by contacting the corresponding author via email. Description of the data and specific instructions for gaining access will be listed in a publicly-available format in the repository. The data will be made available in this format at the time that the paper describing the trial outcome is published, upon MH’s graduation from her PhD, or 2 years after the end of data collection (whichever comes first). Obtained results will be communicated to participants, clinicians, and the public through newsletters, talks and press releases. Materials that were modified or developed specifically for the purpose of the current trial, as well as data management plan, will be available from the project’s webpage at Open Science Framework upon completion of data collection for the trial.

## Abbreviations

BPDS: Bath CRPS Body Perception Disturbance Scale
BPI: Brief Pain Inventory
CRPS: Complex Regional Pain Syndrome
FTP: Finger-To-Palm distance
LTFU1: Long Term Follow-Up 1 (week 19) by post
LTFU2: Long Term Follow-Up 2 (week 31) by post
MDT: Mechanical Detection Threshold
MET: Movement Execution Time
MIT: Movement Initiation Time
MPT: Mechanical Pain Threshold
NRS: Numerical Rating Scale
PA: Prism Adaptation
PSE: Point of Subjective Equality
PSS: Point of Subjective Simultaneity
QST: Quantitative Sensory Testing
RS1: Research Session 1 (week 1)
RS2: Research Session 2 (week 4)
RS3: Research Session 3 (week 7)
RS4: Research Session 4 (week 11)
RSDSA: Reflex Sympathetic Dystrophy Syndrome Association
RT: Reaction Time
TOJ: Temporal Order Judgement
VF: Visual Field
